## Abstract

Dementia causes deterioration in cognitive and physical functions. The scope of this study is to investigate the effect of different exercise programs on cognitive functions and functionality of persons suffering from mild Alzheimer’s disease (AD) by generating information on the exercise types and their parameters. A randomized controlled trial (RCT) will be performed involving aerobic and resistance exercise interventions, taking place both at the sample collection center and at home. Participants will be randomly divided into two different intervention groups and a control group. All groups will be assessed twice; once at baseline and once after 12 weeks. The primary outcome shall comprise the effect of exercise programs on cognitive functions using cognitive testing, such as Addenbrooke’s Cognitive Examination—Revisited (ACE-R), Mini Mental State Examination (MMSE), Trail Making Test A-Β (TMT A-B), and Digit Span Test (DST): Digit Span Forward (DSF) and Digit Span Backward (DSB). The effect on functionality will be assessed using the Senior Fitness Test (SFT), Berg Balance Scale (BBS), and Instrumental Activities of Daily Living Scale (IADL) questionnaire. Secondary outcomes include the effect of exercise on depression using the Geriatric Depression Scale-15 (GDS-15), on physical activity using the International Physical Activity Questionnaire (IPAQ), as well as the participants’ compliance with the intervention. This study will investigate the possible effect of intervention of different exercise types and the comparison between them. Exercise forms a low-cost and reduced-risk intervention.

## 1. Introduction

Aging, as an inevitable fact of human life, is a dynamic and evolving process involving morphological, functional, biochemical, and psychological changes [1]. It is estimated that between 2015 and 2050, the number of people over 60 years old will have increased from 900 million to 2 billion globally [1,2]. As the number of elderly people increases worldwide, so does the number of people suffering from dementia, which poses a serious epidemic problem to humanity, whilst becoming a major social and public health issue [2,3,4,5].

There are several types of dementia related to different causes (changes in the brain) such as Alzheimer’s disease (accumulation of the abnormal proteins beta-amyloid and phosphorylated tau, as well as the degeneration of nerve cells), vascular dementia (vascular pathology), frontotemporal dementia (frontotemporal lobar degeneration), dementia with Lewy bodies, and mixed types [5,6]. Although dementia is common in the elderly, it is not a normal part of aging [5]. There is a small percentage, around 10%, in which dementia is detected in middle age and is due to so-called early-onset Alzheimer’s disease [6]. Initially, there is episodic loss of short-term memory, then gradually, the memory is lost completely [6]. Judgment disorder, disorientation, and language disorder follow [6]. As the disease progresses, the decline in cognitive and physical function often accompanies depression, apathy, agitation, psychosis, sleep disorders, as well as extrapyramidal symptoms [6].

There have been multi-domain lifestyle interventions to reduce and prevent dementia risk, which include pharmacological and non-pharmacological treatments such as exercise, Mediterranean diet, physical activity, etc. [7].

In recent years, there has been a particular interest in the role of physical exercise as prevention as well as a therapeutic strategy for the management of persons suffering from dementia [8,9]. Exercise has been shown to have positive effects on functionality, fall prevention and reduction, cognition, sleep disturbances, mood, and quality of life in dementia patients [10]. Usually, the recommendation for exercise in patients with AD is made without specifying types, frequency, or intensity of exercise [10,11]. However, both the exercise burden and the effect on the patient vary significantly from person to person [10].

The benefits of aerobic exercise have been demonstrated in several studies, although we do not have enough studies on the benefits of resistance exercise in people with dementia [1,9,11].

The purpose of this study is to investigate the effect of exercise on the cognitive and physical functions in patients with Alzheimer’s disease and to provide information on appropriate types of exercise and its parameters in order to maintain and improve cognition and physical functions.

## 2. Material and Methods

### 2.1. Source of Data

The present research is a double-blind, randomized prospective intervention study on the effect of exercise on cognitive functions and functionality in persons with dementia. This protocol describes a 12-week randomized clinical trial control applied to patients with mild dementia (Alzheimer’s Disease). The main hypothesis of the study aims to establish not only the effect of exercise on the cognitive and physical function of patients but also the magnitude of that effect on cognitive and physical functioning in relation to the various exercise protocols.

### 2.2. Participants and Eligibility

The sample of the study population will be selected by the method of purposive sampling, observing the rules of appropriateness and adequacy.

In order to estimate the sample of patients required for any statistical relation to be established as significant, we perform a priori power analysis using the software GPower 3.1. The parameters applied included: (a) alpha level of 0.05 (b) statistical power at least of >80%, (c) the effect size or else the magnitude of the effect of the exercise is expected to be small to moderate and was determined (f = 0.23–0.24). The effect size (ES) is estimated based on previous studies on the cognitive effects of combined aerobic and strength training and single aerobic training using a similar intervention [12,13,14]. Since we are going to study multiple outcomes (cognitive function and functionality), we used the weakest exercise outcome association for sample size calculation. With the above parameters and the fact that the present study provides information for three groups, the calculator showed us that by using 171–186 participants in total, or 57–62 individuals per group, we could secure a meaningful statistical power 80% for all the assessments performed.

Participants will be recruited with the assistance of the Amarousion Day Center of the Alzheimer Society of Athens as well as from the outpatient clinic of the Athens General Hospital “G. Gennimatas”. Potential study participants are to be notified by the center’s physician. The participants will be persons with mild Alzheimer’s disease which was determined in accordance with the diagnosis (DSM-IV and NINCDS/ADRDA diagnostic criteria) [15,16].

All study participants will receive full and clear information, both verbally and in writing, explaining the purpose of the study, data confidentiality and the voluntary nature of participation without financial incentive. They will also be informed that they can withdraw their participation from the research at any time. Whilst each question will be explained, the participants will be able to call the main researcher anonymously at all times, whenever they are in need of more information or clarifications. When the study is completed, the participants will be informed on the results of the study, if they so wish. As soon as all patients have been fully informed, they will be requested to provide written consent of participation in this study. The preparation costs and relevant expenses shall be borne by the researchers.

### 2.3. Participant Inclusion and Exclusion Criteria

Participants meeting the following criteria will be able to participate in the research: Age ≥ 65, diagnosis of mild AD with MMSE score: 20–24/30, without hearing and/or vision impairment which might complicate their participation. The participant must be able to walk to the intervention place, have a caregiver, as well as medical consent to participate in the exercise routine. The participant must not currently participate in any other exercise program, be on stable medication for at least 2 months, and must possess ability of consent according to the treating physician and the treatment team.

Participants will be excluded if they suffer from other neurological disease and severe diseases which would not allow participation in exercise (severe psychiatric illnesses, uncontrolled arterial hypertension, severe cardiorespiratory problems, severe musculoskeletal problems), cancer, surgery during the previous year, severe vision and/or hearing problems, or alcohol and/or drug abuse.

### 2.4. Randomization and Blinding

The randomization will be performed by an independent researcher, who will remain hidden from the rest of the research team involved in the interventions, the assessments, the collection of outcome measurements, and the analysis of data. Prior to the baseline assessment, the participants are to be randomly assigned to one of three groups, A, B, and C (two exercise intervention groups and one usual care—control group), by using random number generator. The allocation sequence will be concealed from the researchers related to the study and the intervention will be assigned using sealed envelopes based on order of recruitment. The random allocation will not appear on the assessment forms and the participants’ names will be replaced by code numbers. 

All participants will be assessed by means of two evaluations prior to the start of the intervention and immediately after the completion of the program (12 weeks) with an optional 12-week extension. Professionals participating in the intervention program will not participate in the physical assessment.

During the assessment, in addition to the demographic data, the following data will be collected: somatometric characteristics (height–weight–body mass index), medication, serious illnesses, any incidents involving falling during the last six months, arterial pressure, heart pulses, oxygen saturation, smoking habits, and level of education. Demographics will only be recorded during the initial assessment.

During each assessment, participants and examiners are not allowed to provide or request any information regarding the exercise program being performed. Furthermore, the assessors will be blinded to previous test results. All the above will be included in the study flowchart (Figure 1) in accordance with the CONSORT guidelines.

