Aerobic Exercise: The type of aerobic exercise in the present study will involve walking at moderate intensity. Walking is the primary mode of physical activity, given its widespread popularity and ease of administration to a broad segment of the elderly population [63]. We focus on moderate training, as studies indicate the greatest effects compared to light or vigorous exercise [64]. The frequency of aerobic exercise will amount to 30 min, 5 days per week. Moderate intensity is defined as 64–76% of the HRmax which is the most commonly used indicator for determining the intensity of aerobic exercise [4,11,56]. The maximum heart rate is calculated according to the type: HRmax = 220 − age.

Moderate intensity control will be monitored based on the participant’s Borg scale of subjective perception of fatigue during exercise by the caregiver at home. Specifically, exercise intensity is graded using a 6–20 category ratio scale (Borg Rating of Perceived Exertion (BRPE) Scale 6–20) according to fatigue and breathlessness. Medium volume is set to approximately 13 [56,65,66]. Caregivers will supervise all exercise sessions since these take place at home, whilst the sessions will be monitored by physiotherapists once a week for the first 2 weeks and subsequently once a month.

Resistance Exercise: The resistance exercise in the study will target the major muscle groups of the body and will be performed with limb weights at moderate intensity according to 50–69% of a maximum repetition (% 1-RM) [56]. The intervention will include 2 sets of 10 exercises of the main muscle groups starting with 8 repetitions which will progressively be increased to 12 repetitions. The frequency of resistance training will amount to three workouts per week (every 48 h), with a duration of 40–45 min per session, with a break of 1–3 min between sets [56,60,61,62,67,68]. Of the three exercise sessions, two will take place at the recruitment center under the supervision of the physiotherapist and one at home under the supervision of the caregiver. The moderate intensity control will additionally be monitored based on the scale Borg (Rating of Perceived Exertion). During the first two weeks, the physiotherapists will supervise the exercise at home once a week and subsequently once a month.

**Intervention group B:** Resistance exercise program

Intervention group B will perform the same resistance exercise program as intervention group A.

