The aerobic exercise program and the resistance exercise program will both be followed progressively. Both intervention programs will also include warm-up and cool-down exercises lasting 5–10 min, respectively, with active exercises for the head, limbs, and torso, as well as stretching.

The interventions were selected and designed so as to provide the possibility of easy reproduction at home, promoting an active lifestyle which could be maintained even after the end of the study. Furthermore, the intervention program including illustrated instructions will be made available to the participants and must be followed for 12 weeks.

Strategies for monitoring and adhering to the intervention will comprise one (1) experienced physiotherapist’s visit to the patient’s home during the first two (2) weeks and then one (1) visit per month, one (1) phone call once a week during the first month, and then one (1) phone call per month. Participants and their caregivers will complete an exercise diary form.

Home visits and telephone communications are intended firstly to ensure that the exercises are performed correctly and safely according to the protocol, secondly to resolve any problems, and thirdly to encourage the participant’s effort.

**Control group C:** No participation in any exercise program

The control group participants will be encouraged to maintain their usual daily activity without engaging in any exercise program. Team members who deviate from their daily routine by following any physical exercise program will be excluded from the team.

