## 5. Statistical Analysis

Descriptive and inferential statistical analysis will be carried out. The normality of the variables under consideration will be tested with the Shapiro–Wilk test. Possible dependencies between qualitative variables and categorical scales characteristics of the three different groups will be investigated using Pearson’s chi-squared test (χ^2^).

A paired t-test or the non-parametric Wilcoxon signed-rank test was performed to analyze whether there was any significant improvement in the cognitive function and mood (ACE-R, MMSE, TMT A-B, DST F-B, and GDS-15) and functionality (SFT, BBS, IADL, and IPAQ) after the subjects had completed the 12 weeks intervention of the two different exercise programs.

In order to investigate differences between groups, at baseline and after the intervention, one-way ANOVA F-tests, or Kruskal–Wallis tests for more than two independent samples will be carried out for all the mentioned variables, both at baseline and after the intervention (12 weeks). Bonferroni correction was applied to adjust for multiple pair-wise comparisons of the means for the main effects.

Pearson’s or Spearman’s correlation tests for the total changes from baseline will be applied accordingly to normality test. Variables correlated significantly will be used for further multivariate analysis. To further analyze the relationship between the changes of outcome measures, a multivariate linear regression analysis will also be applied for the total changes from baseline, in order to clarify the effect of exercise in cognitive function and functional performance. If group differences are observed at baseline, those variables are included as covariates in further analyses. To assess the effect on the primary and secondary outcome measures, analysis of covariance (ANCOVA) is used with cognitive domain scores on the post-tests as dependent variables, pre-test scores as covariates, and group (combined aerobic and resistance exercise program, single resistance exercise program, control) as the between-subject factor.

Statistical analyses will be carried out using the statistical software package SPSS 24.0 for Windows (SPSS Inc., Chicago, IL, USA). *p*-values less than 0.05 are considered statistically significant.

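### Participants are randomised before the baseline assessment with nothing stated to withhold the arm until it is complete, and the double-blind label does not fit exercise against no exercise

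*Protocol article*

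**What the plan says.** All references are to the protocol article.

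- **Order.** Section 2.4: "Prior to the baseline assessment, the participants are to be randomly assigned to one of three groups, A, B, and C". On release of the allocation it says that "the intervention will be assigned using sealed envelopes based on order of recruitment". It does not say when the envelope is opened or when the participant is told the arm.
- **Label.** Section 2.1: "The present research is a double-blind, randomized prospective intervention study".
- **What the arms involve.** Section 4 describes resistance training in both exercise arms, of whose three weekly sessions "two will take place at the recruitment center under the supervision of the physiotherapist and one at home under the supervision of the caregiver". One of these arms adds walking supervised by the caregiver. Exercise diaries are kept. For the third arm, "The control group participants will be encouraged to maintain their usual daily activity without engaging in any exercise program".
- **Masking measures.** Section 2.4 has an independent researcher do the randomisation and conceals the sequence. It adds: "The random allocation will not appear on the assessment forms and the participants’ names will be replaced by code numbers". It also bars talk about the programme during each assessment, blinds assessors to previous results, and keeps intervention staff out of the physical assessment.
- **Use of baseline scores.** The ANCOVA in Section 5 takes "pre-test scores as covariates, and group" as its terms. Section 5 also plans paired pre-post tests and analyses of change from baseline, and it adds as covariates any variables on which the groups differ at baseline.

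**The concern.** A baseline covariate is safe to adjust for because it is fixed before allocation, or at least before anyone can react to allocation. Once the arm is known, a baseline score becomes a post-randomisation measurement. Someone who knows that a training programme is coming, or that none is, may put in a different effort on a fitness or balance test, or answer differently about mood, daily activities or physical activity. Adjusting for such a score carries the distortion into the treatment estimate. The rule that adds covariates when groups differ at baseline makes this worse, because a difference caused by allocation would be treated as chance imbalance.

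A second route is loss. A person who learns the arm and leaves before baseline has no pre-test score and falls out of every change and ANCOVA analysis. Only the MMSE used for eligibility (Section 2.3) might exist for such a person.

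The label is a separate matter and does not depend on envelope timing. IADL belongs to the primary objective, and GDS-15 and IPAQ are secondary. All three are completed by interview (Section 3.1). Readers will give such answers more weight in a double-blind trial than in one where the respondent knows the treatment.

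**Working it through.** **1. Who can be blind.** Set Section 2.1 beside Section 4. Participants either train with weights several times a week or are told not to join any exercise programme. Caregivers are trained to supervise the home sessions, and physiotherapists deliver the centre sessions. None of these three can be unaware of exercise against no exercise. The measures in Section 2.4 act on the sequence, the forms and the assessors. They mask the assessor and leave the participant's own knowledge untouched.

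**2. The plan's own figure.** Section 2.2 gives 171–186 participants for three groups, alpha 0.05, power 80%, f = 0.23–0.24. The check uses a noncentral F test with 2 and N − 3 degrees of freedom and noncentrality N·f²:

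- f = 0.24, N = 171: 171 × 0.0576 = 9.85, power 80.2%
- f = 0.23, N = 186: 186 × 0.0529 = 9.84, power 80.2%

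Both figures reproduce, also with one covariate in the model. Changing the order of randomisation and baseline leaves them as they are.

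**3. Bias if the arm is known at baseline.** The ANCOVA contrast is

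(post-test mean, exercise − control) − b × (baseline mean, exercise − control),

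where b is the pre-post slope. Suppose knowing the arm lowers measured baseline in the exercise arms by d SD and leaves the post-test unchanged. The contrast is then biased by +b·d, in favour of exercise. If exercise participants score higher at baseline instead, the bias is −b·d. A raw comparison of change scores takes the full d, and a comparison of 12-week scores alone takes none of it.

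Inputs b and d are assumptions; the document gives neither.

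| d (SD) | b = 0.5 | b = 0.7 |
|---|---|---|
| 0.1 | 0.05 | 0.07 |
| 0.2 | 0.10 | 0.14 |
| 0.3 | 0.15 | 0.21 |

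**4. False-positive rate of the group F test.** Simulation with 60 per arm, no true effect, both exercise arms lowered by d at baseline, 1,500 runs per cell. The simulation error near 5% is √(0.05 × 0.95 / 1500) = 0.6 percentage points.

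| d (SD) | b = 0.5 | b = 0.7 |
|---|---|---|
| 0 | 5.2% | 4.7% |
| 0.1 | 5.8% | 6.9% |
| 0.2 | 9.0% | 16.9% |
| 0.3 | 15.0% | 32.5% |

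A shift of 0.1 SD at the lower slope cannot be told apart from no shift. Larger shifts matter.

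**The case against.** The strongest reply is that assignment is not disclosure. A sequence can be fixed, and even an envelope allotted, before baseline without the participant knowing the arm. If the envelope is opened afterwards, neither the bias nor the selective loss arises, and a condensed article may leave that detail to the full protocol. This stands as a limit: the bias is conditional. It does not clear the text, which states the weaker order outright and says nothing to withhold the arm.

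The assessor side is also well protected, and that stands too. What remains open is the knowledge held by participants and caregivers.

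One could say that double-blind here means assessors and analysts. The article does not define it so, and most readers take the term to include the participant.

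Three stronger readings are tempting and are not supported:

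- **That the ban on discussing the programme shows participants know their arm at baseline.** The ban concerns a programme under way, which fits the 12-week visit. It is ordinary assessor masking.
- **That cognitive testing lacks staff separation, because Section 2.4 says only that** "Professionals participating in the intervention program will not participate in the physical assessment"**.** Physiotherapists deliver the exercise (Section 4), whereas a neuropsychologist or psychologist does the cognitive tests (Section 3). The sentence is needed where physiotherapists stand on both sides, and the text shows no gap elsewhere.
- **That the bias is a known share of the planned effect.** With f = 0.23, the largest difference between arms is 3f/√2 = 0.49 SD if both exercise arms have equal means, and √6·f = 0.56 SD if the three means are evenly spaced. A bias of 0.07–0.14 SD would be 14–29% of the first or 12–25% of the second. The document fixes neither the pattern of means nor the shift.

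Finally, the ANCOVA sentence in Section 5 names cognitive domain scores as the dependent variables, while the measures most open to distortion are functional and interview ones. The same sentence, however, presents ANCOVA as the analysis for all primary and secondary outcomes.

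**Conclusion.** Two points hold. First, Section 2.4 states an order, randomisation before baseline, that exposes the baseline scores to knowledge of the arm, and nothing in the article closes that exposure for participants and caregivers. Second, double-blind in Section 2.1 is wrong for this comparison; assessor-blinded is the most that the described measures support.

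The consequence of the first point is conditional on disclosure before baseline. Given that, effort-dependent and interview baselines (SFT, BBS, IADL, GDS-15, IPAQ) may be distorted, and the ANCOVA contrast moves by about slope times shift. The illustrative 0.07–0.14 SD rests on an assumed slope of 0.7, an assumed shift of 0.1–0.2 SD, and no effect of the shift on the post-test. Its direction is not determined by the document. It shows that a modest shift would matter; it does not measure a defect in this trial. The correction should be made because it is cheap. Nothing here shows that the trial is invalid.

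**What to change.** 1. **Section 2.4.** Change the order to: consent, eligibility, complete baseline assessment, then randomise and open the next envelope. If disclosure already follows baseline in practice, say so in one sentence.
2. **Participants already enrolled.** Record for each one the order used and the date on which the arm was disclosed.
3. **Section 2.1.** Replace double-blind with: *assessor-blinded; participants, caregivers and treating physiotherapists are not blinded*.
4. **Interpretation.** State that IADL, GDS-15 and IPAQ are interview outcomes from unblinded respondents. Section 3.1 already says that they are taken by interview, so only the unblinded part is new.

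The cost is one re-ordered step and a few wording changes, with no extra staff and no change in sample size. There is one small downside. Section 8 reports that COVID-19 restrictions hampered sample collection, so recruitment may have begun, and the trial would then contain two procedures. Recording the order does not repair the earlier baselines, but it lets the two sets of participants be told apart in the analysis.

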## 8. Strengths and Limitations of This Study

According to what we know, this randomized controlled trial (RCT) will be the first study to examine the effect of aerobic exercise combined with resistance exercise in comparison to resistance exercise only, in patients with dementia.It will also be the first study in Greece to examine the effect of aerobic exercise combined with resistance exercise in comparison to resistance exercise only in patients with dementia both in the center and at home.The intervention program is comprehensive and well-structured as well as easy to perform, without the necessity for specialized and expensive equipment.During the study, the COVID-19 restrictions created difficulties in the sample collection and, therefore, the duration of the study may have to be extended.

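### Sex and recruiting source are adjusted for only if a baseline difference happens to appear; both should be prespecified terms in the ANCOVA

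*Protocol article*

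**What the plan says.** **Allocation (section 2.4).** By the protocol article, "the participants are to be randomly assigned to one of three groups, A, B, and C", and this is done "by using random number generator. The allocation sequence will be concealed from the researchers related to the study and the intervention will be assigned" from sealed envelopes in recruitment order. The text states no allocation ratio, blocking or stratification, and does not say that they are absent.

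**Sample (section 2.2).** The calculation uses an "alpha level of 0.05", "statistical power at least of >80"%, and an effect "expected to be small to moderate and was determined (f = 0.23–0.24"). It concludes that 80% power is reached "by using 171–186 participants in total, or 57–62 individuals per group". Recruitment is through a day centre "as well as from the outpatient clinic of the Athens General Hospital".

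**Sex-dependent measures (section 3.1.2).** IADL leaves out three of its eight domains for men, so the maximum is 8 for women and 5 for men. In the arm-curl item of the Senior Fitness Test, women lift 2 kg and men 3.5 kg. Section 3 lists both instruments under the primary objective.

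**Analysis (section 5).** The ANCOVA has the post-test as response, the pre-test as covariate and group as factor. It is introduced for primary and secondary outcomes, but the dependent variables it names are cognitive domain scores. Other variables become covariates only if the groups differ on them at baseline. Separately, one-way ANOVA or Kruskal–Wallis tests compare all outcomes after the intervention without adjustment. Recruiting source appears neither in section 5 nor in the list of baseline data in section 2.4.

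**The concern.** Two characteristics known before randomisation may well be related to the outcomes. Sex fixes the range of IADL. Source may reflect a different case mix. Under section 5 each enters the model only if a baseline difference is noticed. This has three consequences.

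- The model for the primary outcomes is not fixed before the data are seen.
- Prognostic information is discarded whenever the groups look balanced, although adjustment gains precision then too.
- Source cannot trigger the rule at all unless it is recorded, and the article does not list it.

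At stake are some precision and a data-dependent model, not the validity of the randomised comparison.

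**Working it through.** **1. The plan's own sample size.** One-way ANOVA F test, k = 3, alpha 0.05, noncentrality λ = f²N, error degrees of freedom N − 3.

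- f = 0.24, N = 171: λ = 0.0576 × 171 = 9.85, power 80.18%.
- f = 0.23, N = 186: λ = 0.0529 × 186 = 9.84, power 80.19%.

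The stated figures reproduce exactly: 57 per group belongs to f = 0.24 and 62 to f = 0.23.

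**2. How often the conditional rule would act.** The article does not define an observed baseline difference. Suppose it means p < 0.05, the threshold in section 5. Under randomisation the null hypothesis holds for every baseline factor, so a given factor is flagged in about 5% of trials. At least one of two independent factors is flagged in about 1 − 0.95² = 9.75%. In roughly nine trials of ten, neither sex nor source would be adjusted for.

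The prevalence of either factor is not given. For assumed values of 30–65% and three groups of 57 or 62, simulation puts the largest between-group difference at 15 percentage points or more in 15–25% of allocations. A rule that fires in about 5% misses most of these.

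**3. What sex can do to IADL.** The maximum differs by 8 − 5 = 3 points. If two groups differ by 15 percentage points in the proportion of women, their highest attainable mean scores differ by 0.15 × 3 = 0.45 points. This is an illustration at the ceiling for the unadjusted post-intervention comparison. Pre-test adjustment would remove part of it.

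**4. Gain from prespecifying both terms.** If sex and source explain a share R² of the variance left after the pre-test score, the effect size becomes f/√(1 − R²). The documents give no R²; 5–10% is assumed.

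| | R² = 0 | R² = 5% | R² = 10% |
|---|---|---|---|
| f = 0.24, N = 171 | 80.2% | 82.3% (λ = 9.85/0.95 = 10.37) | 84.4% (λ = 9.85/0.90 = 10.94) |
| f = 0.23, N = 186 | 80.2% | 82.3% (λ = 10.36) | 84.4% (λ = 10.93) |

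**5. Cost.** Two error degrees of freedom. At R² = 0, with the pre-test score in the model, power moves from 80.17% to 80.16% (N = 171) and from 80.19% to 80.18% (N = 186).

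**6. Allocation, if it is simple randomisation on one list.** The SD of one group's size is √(N × 1/3 × 2/3): 6.2 at N = 171 and 6.4 at N = 186. By simulation the median gap between largest and smallest group is 12, with a 95th percentile of 25–26. Average power falls from 80.2% to 79.8%, about 0.35 points; the 2.5th percentile over allocations is about 74–75%. With permuted blocks of 6 (an assumed size) in two source strata, an unfinished block leaves a gap of at most 2 per stratum, so at most 4 overall.

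**The case against.** The strongest reply is that the plan already covers this. The ANCOVA adjusts for the pre-test score, and a man's IADL is scored out of 5 at both visits, so much of the sex effect is absorbed. The baseline rule covers visible imbalance. Chance imbalance does not bias a randomised comparison. The power gain depends on an R² for which the documents give no evidence.

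Most of this stands, and it is why the gain is modest. It does not rescue the conditional rule, which still leaves the model to the data. It is also unclear whether IADL receives the pre-test adjustment, since the ANCOVA sentence names only cognitive domain scores as dependent variables.

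A reader might infer three stronger points, none of which the documents support.

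- **That there are no blocks or strata.** A random number generator can produce a blocked or stratified list, and a condensed article may leave that detail to the full protocol. Envelopes in recruitment order suggest a single list over both sources, but do not settle it.
- **That the allocation cannot deliver the stated group sizes.** The range 57–62 is the requirement at two effect sizes, not a tolerance band for realised groups. Simple randomisation is a valid method and barely changes average power.
- **That recruitment was interrupted and the groups are unbalanced over time.** Section 8 says only that "the COVID-19 restrictions created difficulties in the sample collection" and that the study may be extended. Slow recruitment does not increase the expected imbalance under simple randomisation.

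**Conclusion.** The point holds as an analysis improvement. Sex and recruiting source should be fixed in the ANCOVA in advance and not left to an observed baseline difference. The benefit is a model that does not depend on the data, and power of about 82–84% in place of 80% if the two terms explain 5–10% of the variance remaining after the pre-test score. That share is assumed; if it is nil, the loss is about 0.01 percentage points of power. The case is clearest for IADL, because of its sex-specific range. For source it rests on the plausible but undocumented premise that day-centre and hospital patients differ.

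No error in the randomisation is demonstrated. Allocation is a secondary and conditional matter.

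**What to change.** - **Section 2.4:** add recruiting source to the baseline data, including for participants already enrolled.
- **Section 5:** for every primary outcome, state an ANCOVA with the pre-test score, group, sex and recruiting source as prespecified terms, for all participants. Delete the rule that adds covariates after baseline differences are observed. Make explicit that the functionality measures are included.
- **Optional, for participants not yet randomised:** if the list is not already restricted, the independent researcher could use permuted blocks of randomly varying size within recruiting source, with block sizes kept from the team. If blocks or strata already exist, one sentence saying so is enough.

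The analysis change costs one recorded variable, a short edit and two degrees of freedom. The optional allocation change costs new lists and envelopes for each source, and slight predictability near the end of a block, because those delivering the exercise know the groups.
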